#### Missing data

Analysis of the economic data will use an intention-to-treat approach that includes service use, cost and health benefit data for all services users, regardless of whether they completed the planned follow-up and all the measures used at assessment. It is highly likely that data will be missing, either from loss to follow-up or incomplete data collection.

Single imputation will be used to impute missing baseline data. This simple approach is appropriate for baseline data, although in reality this is unlikely to have a significant impact as participants who have missing data at baseline are less likely to have follow-up data.^26 27^ Baseline variables are observed at entry to the trial and vary by the individual rather than random allocation to trial arms or values at follow-up. In contrast follow-up values for clinical and economic measures may be dependent on trial allocation and baseline. Accordingly, single imputation for baseline measures of cost, utility and clinical indicators ensures the estimated values are independent of treatment allocation and follow-up values. Single imputation is likely to be more efficient than multiple imputation. Multiple imputation (MI) will be used to impute missing follow-up data for costs and QALYs, which assumes that the data are missing at random (conditional on observed responses to clinical and economic measures and baseline covariates); MI of both costs and QALYs is recognised as an appropriate approach to deal with missing observation and missing follow-up data.^26^ Missing values will be imputed for each follow-up point. All missing follow-up cost and utility data will be assumed to be missing at random. To make best use of available data, we plan to impute costs by category (inpatient, outpatient and primary/community care) and utility by individual EQ-5D domain (mobility, self-care, usual activities, pain/discomfort and anxiety/depression). A balance is required between including all items and the stability of the imputation model if there is a high level of missing data. The stability of the model reduces as the number of variables with missing data increases. If feasible, all individual items in each cost category will be included in the imputation model. Total costs and QALYs (baseline to follow-up) will be generated using Stata passive estimation commands. The final imputation plan will be refined following a review of missing data (exploration of whether there are any patterns of missingness) and according to the patterns of service use and EQ-5D data. Two sensitivity analyses will explore whether the results vary by approach taken to missing data. The first will use complete case analysis. The second will use a pattern mixture approach that assumes compliance and clinical outcomes are systematically worse in people with missing or with incomplete follow-up.^26 28^ The specification of the analysis will be finalised after review of the complete and missing data patterns and discussion with clinical experts about plausible assumptions. If appropriate this analysis will identify the threshold values of compliance and clinical outcome that would lead to a change in conclusions about the relative cost-effectiveness of the within trial economic analysis.

Multiple imputations will be conducted in Stata V.15, using predictive mean matching and sequential chained equations. Regression models used to impute missing data will be based on key covariates associated with costs or health benefits. A long list of potential covariates was identified from a recent systematic review of economic evaluations in the population undergoing cardiac rehabilitation and the baseline data collected within this randomised controlled trial (see online supplementary material). Discussions with clinical experts in the team will be used to assess the relevance and logic of using these variables as covariates in our analysis. This approach will be supplemented with pooled descriptive analyses and regression analyses to identify the final set of covariates.^6^ A list of potential covariates is included in the online supplementary material.

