The PATHWAY Group MCT multicentre, single-blind, randomised controlled trial aims to evaluate the effectiveness and cost-effectiveness of group-based metacognitive therapy for CR patients with elevated anxiety and/or depressive symptoms.^5^ Details of the main trial study protocol are available elsewhere.^5^ In brief, participants were recruited from patients with heart disease and referred for CR, in five UK National Health Service (NHS) Trusts. Trial participants had to meet CR eligibility criteria, score 8 or more on either the anxiety and/or depression subscale of the Hospital Anxiety and Depression Scale (HADS), be aged 18 years old or more and able to read, understand and complete questionnaires in English. Patients who gave informed consent to participate in the trial completed baseline assessments and were randomised via telephone link to Manchester Clinical Trials Unit. Participants were allocated to the intervention/comparator arms in a 1:1 ratio via a minimisation algorithm (incorporating a random component) to maximise balance between the two arms on gender, HADS score and hospital site. Participants randomised to the intervention arm received 6 weekly sessions of group-based metacognitive therapy delivered by either CR professionals or research nurses. The intervention and control groups were both offered in the usual CR programme within their Trust. The primary outcome is severity of anxiety and depressive symptoms at 4-month follow-up measured by the HADS total score.^13^ Secondary outcomes are severity of anxiety/depression at 12-month follow-up, health status, severity of post-traumatic stress symptoms, strength of metacognitive beliefs and service use at 4-month and 12-month follow-up. The PATHWAY Group MCT trial is part of a wider NIHR (National Institute for Health Research) programme grant for applied research, which began in August 2014 and with an end date of February 2021.

The aim of the economic evaluation component of the PATHWAY Group MCT trial is to estimate the cost-effectiveness of the addition of MCT intervention to CR for patients with elevated anxiety and/or depression symptoms, in a UK setting from a health and social care perspective. This will consist of a within trial analysis using patient-level data collected during baseline and follow-up study time points, and an economic model synthesising data from the trial and wider literature.

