### Within-trial analysis

The analysis will use individual patient-level service use and health benefit data from all participants recruited and allocated to a management arm in the PATHWAY Group MCT trial (n=332). The trial opened for recruitment in July 2015 and closed in January 2018, follow-up finished in February 2019. The economic analysis of trial data will begin in April 2020 and will complete by September 2020. The analysis will compare the addition of group-based MCT to usual CR versus usual CR alone (standard practice) for individuals with elevated symptoms of depression and/or anxiety. The study sample for the economic evaluation is all participants randomised to receive the group-based MCT plus usual CR, or usual CR only. In brief, participants were people eligible and offered (referred to) CR as per NHS trust protocol, with a HADS score of 8 or more on the anxiety and/or depression subscale. The intervention, usual care and participant inclusion and exclusion criteria are summarised and described in detail in the trial protocol.^5^ Usual CR (dependant on NHS site) includes varying degrees, psychological interventions to address distress such as relaxation, stress management and some cognitive challenging.

The time horizon of the within-trial primary cost-effectiveness analysis will be 12 months, to incorporate sufficient time for any impact of MCT on service use, subsequent costs and health benefit. This differs to the primary clinical effectiveness time horizon, which will be 4 months (note, a sensitivity analysis will look at cost-effectiveness at 4-month follow-up).^5^

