#### Outcomes

The measure of health benefit for the primary analysis will be the quality-adjusted life-year (QALY). This will be estimated from the EQ-5D-5L health status measure completed at baseline and 4-month and 12-month follow-up. The EQ-5D is a validated, generic health status measure, allowing for the comparison of health benefits across different disease areas. The EQ-5D has been shown to be a valid and responsive measure of health in CR patients.^17^ Furthermore, the QALY and the EQ-5D are the measures recommended for economic evaluations by NICE.^18^

The EQ-5D-5L captures the following five domains of health status: mobility, self-care, usual activity, pain/distress and anxiety/depression. Each domain is rated on a 5-point scale of levels: no problems, slight problems, some problems, severe problems or unable to do activity. Resulting health status profiles will be converted to utility values using the published utility tariffs and methods recommended by NICE at the time of analysis. An EQ-5D-5L valuation set is available that reflects the preferences of members of the public in England for health states defined by the EQ-5D-5L.^19^ However, concerns have been raised during the quality assurance of this value set and currently, NICE recommend that the crosswalk algorithm used to map from the EQ-5D-3L to the EQ-5D-5L continues to be used.^20^ The economic evaluation will use the value set recommended by NICE at the time of analysis. The use of alternative value sets will be investigated in the sensitivity analysis.

Total QALYs will be estimated as follows:

$$QALY=\sum \left(\left[U_{i}+U_{i+1})/2\right]\times (t_{i+1}-t_{i}\right)$$

Here, U=utility value and t=time between assessments. The time between assessments is the time from baseline data collection to follow-up.

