#### Identifying data sources

Data from the trial will likely inform the majority of short-term parameters within the base case economic model. This will be supplemented with structured literature reviews to identify parameters and alternative inputs for the short-term that might help to inform analyses in alternative settings and population. Examples of inputs that will be identified will include uptake rates in cardiac rehabilitation, utilities, costs, mortality and likelihood of depression/anxiety relapse and remission. Evidence relevant to the cardiac population will be prioritised. Parameter tables will be drafted and shared with the clinical advisers on the project to discuss and assess clinical validity prior to use in the model. Data uncertainty will be explored in the sensitivity analysis outlined below.

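### The rule that all missing follow-up costs and utilities are missing at random makes no exception for participants who die, and its method can only give them living values

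*Protocol article*

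**What the plan says.** The within-trial analysis covers everyone randomised (332 participants, allocated 1:1). The Missing data section keeps them all in, "regardless of whether they completed the planned follow-up and all the measures used at assessment". QALYs come from the EQ-5D-5L; the Outcomes section says "This will be estimated from the EQ-5D-5L health status measure completed at baseline and 4-month and 12-month follow-up".

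For gaps at follow-up the Missing data section states: "All missing follow-up cost and utility data will be assumed to be missing at random". It adds: "Missing values will be imputed for each follow-up point". Costs are to be imputed by category and utility by each of the five EQ-5D domains, with predictive mean matching and chained equations. Totals are then derived from the imputed components.

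On why data may be missing, the section says: "It is highly likely that data will be missing, either from loss to follow-up or incomplete data collection". Death is not named there or anywhere else in the within-trial methods. Mortality is named as an analysis input only for the long-term model, where Identifying data sources lists "utilities, costs, mortality and likelihood of depression/anxiety relapse and remission".

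Two sensitivity analyses address missing data (Missing data; Table 2). One is a complete-case analysis. The other is a pattern-mixture analysis that assumes worse health benefits and higher costs in people with missing data. The section also says that the imputation plan will be refined once patterns of missingness, service use and EQ-5D data have been reviewed.

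**The concern.** These are cardiac patients followed for a year, so deaths are foreseeable, although the article gives no number. A participant who dies before month 4 or month 12 returns no form at that visit but still needs a 12-month cost and QALY. Imputation is the only mechanism the article provides for filling that gap.

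After death both values are known: utility is 0 and cost is 0. Treating them as unobserved draws from living responders would take survival out of an outcome meant to combine survival and quality of life, and would add services never used. The QALY error favours whichever arm has more deaths.

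There is a knock-on effect. Model design and validation sets a ±5% agreement check between the long-term model and the trial analysis. If the model counts deaths and the trial analysis imputes through them, the check compares different quantities.

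**Working it through.** The plan has no figure to reproduce, because it states no death count, utility or mean cost. The check has two parts.

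**1. Can the stated method return the right value for a death?**

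- Imputation is at the level of EQ-5D domains. Their levels run from no problems to the most severe level, and none stands for dead.
- Predictive mean matching copies values from observed responders, who were alive when they answered. Every imputed profile is therefore a living one, and every imputed cost is that of a living service user.
- The QALY formula in Outcomes runs between assessments and has no term for a date of death.
- The complete-case analysis uses only people with complete follow-up and data, so as worded it drops those who died.
- The pattern-mixture analysis lowers health benefit among the missing but does not set it to 0. It also assumes higher costs, which is the wrong direction for time after death.

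So if the rule is applied to a death, neither the primary analysis nor either sensitivity analysis gives utility 0 and cost 0.

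**2. How large could the error be?**

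From the article: 332 randomised 1:1, so 332 / 2 = 166 per arm (exact arm sizes are not given); assessments at 0, 4/12 and 1 year; threshold λ = £20 000 per QALY, within the plan's £0 to £30 000 range. Assumed: constant living utility u, and the time of death.

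*Convention A: utility 0 from the date of death.* With r the fraction of the year remaining, excess QALYs per death = u × r. The shift in the arm mean is u × r / 166, multiplied by λ for money.

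| Death at | r | Excess QALY (u = 0.65 to 0.75) | Shift in arm mean QALY | At £20 000 |
|---|---|---|---|---|
| 3 months | 0.75 | 0.488 to 0.563 | 0.0029 to 0.0034 | £59 to £68 |
| 6 months | 0.50 | 0.325 to 0.375 | 0.0020 to 0.0023 | £39 to £45 |
| 9 months | 0.25 | 0.163 to 0.188 | 0.0010 to 0.0011 | £20 to £23 |

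*Convention B: utility 0 at the next scheduled assessment, using the article's own formula.* Take u = 0.7.

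- Imputed as alive throughout: 0.700.
- Death before month 4: (0.7 + 0)/2 × 4/12 = 0.117, an excess of 0.583.
- Death between months 4 and 12: 0.7 × 4/12 + (0.7 + 0)/2 × 8/12 = 0.467, an excess of 0.233.

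In general the excess is 5u/6 for an early death and u/3 for a late one. Over u = 0.5 to 0.8 this is 0.167 to 0.667 QALY. Divided by 166, it is 0.0010 to 0.0040 per net death, or about £20 to £80 per participant.

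*Costs.* Handling uncertainty defines net benefit as outcome times threshold minus cost. Let c be the yearly cost that would be imputed. Under convention A the net-benefit shift per net death is (λu − c) × r / 166, so imputed costs subtract from the QALY error. The article gives no c. At λ = £20 000 the two cancel only if c = £20 000 × 0.65 to 0.75 = £13 000 to £15 000 a year. Below that, the offset is partial. At λ = £0 only the cost error remains, with the opposite sign.

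*Balance.* These are shifts per net death between arms. With equal numbers of deaths at similar times, both arm means are inflated alike and the difference is largely unaffected.

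**The case against.** The strongest reply is that the article never says the dead will be imputed. Its rule concerns missing data, and the same section attributes missing data to loss to follow-up or incomplete collection. If utility and cost after death are known to be 0, they are not missing and the rule does not reach them. Setting them to 0 is also a derivation step that a fuller analysis plan might hold, and the imputation plan is openly not final.

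Much of this stands. A reader might infer that the plan directs living values to be given to participants who died; the text does not support that. A reader might also infer a material bias in the primary result. With no death count, no utilities and no costs in the article, that is not supported either.

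It does not remove the point. The article specifies imputation down to domain and algorithm and states its rule with the word all. Either deaths fall under that rule and are handled wrongly, or they have no rule, and the same sentence cures both. The refinement clause is tied to patterns of missingness, service use and EQ-5D data, and nothing in it points to deaths.

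**Conclusion.** The point holds as a badly bounded rule. As written it makes no exception for deaths within 12 months, its method can only return living utilities and continuing costs, and neither sensitivity analysis corrects that.

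On the QALY side the size is about £20 to £68 per participant per net death at £20 000 per QALY. This assumes utilities of 0.65 to 0.75, deaths at 3 to 9 months and 166 per arm. Utilities of 0.5 to 0.8 with zero at the next assessment give about £20 to £80. In net benefit, wrongly imputed post-death costs offset part of this, and balanced deaths largely cancel. The actual effect is unknown and could be nil. It is a correction worth making because it is cheap and prevents an invalid QALY, but the documents do not establish that the primary result would be wrong without it.

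**What to change.** In Missing data, limit the missing-at-random imputation to values missing while the participant was alive, and add:

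- After death, utility and cost are set to 0, from the date of death if it is recorded and otherwise from the next scheduled assessment.
- Costs between the last returned form and death are genuinely missing and are still imputed.
- Participants who died stay in the complete-case analysis, with these values counted as complete. Table 2 should say so.
- The pattern-mixture assumptions of worse health and higher costs apply only to values missing while alive.

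The cost is a few sentences and a small data step. The article does not say that dates of death were collected, so the fallback is needed. The two conventions give different numbers, so the choice should be fixed before the analysis. Reporting deaths by arm and assessment interval would let readers judge whether the point mattered.

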#### Primary analysis

Costs and health benefit for the primary and sensitivity analyses will be estimated from baseline to end of 12-month follow-up, to estimate the incremental cost-effectiveness of the addition of MCT intervention.

The primary measure of interest for the economic analysis is the incremental cost-effectiveness ratio (ICER). Rather than considering cost and health benefit separately, the ICER is a joint measure of both. It is calculated by dividing the difference in costs (net costs) by the difference in QALYs (net QALYs) between any two interventions. The ICER represents the additional cost of an intervention per additional QALY gained:

$$ICER=\frac{Cost_{MCTinterventionplususualcare}-Cost_{usualcare}}{QALYs_{MCTinterventionplususualcare}-QALYs_{usualcare}}$$

Note that if the intervention is cost saving and produces more QALYs when compared with usual care (ie, it falls in the South East quadrant of the cost-effectiveness plane), an ICER will not be presented as intervention is dominant in such a scenario. Likewise, if intervention is dominated (ICER lies in the North West quadrant of the cost-effectiveness plane) it will be described in this way rather than calculated and presented numerically.

Descriptive analysis and data manipulation will be conducted using SPSS V.25 and the main statistical analyses will be conducted in Stata V.15.

Regression analysis will be used to estimate the net costs and QALYs of MCT. Cost and QALY data may not be normally distributed. Graphical summaries and descriptive statistics will be used to assess the distribution of the pooled cost and QALY data and identify the appropriate regression models for the analysis (eg, generalised linear model with gamma, log distribution for costs). Key covariates will be included in the regression models to control for baseline factors that may influence costs or QALYs. The covariates for these analyses will be identified using the approach outlined for the multiple imputation described in the previous section.

The ICER measures the cost per QALY gained by an intervention which then raises the question of whether the additional cost of a QALY is worth paying for. To help address this, the ICER can be compared with benchmark or threshold values of how much decision-makers may be willing to pay to gain one additional QALY. This is analogous to placing a monetary value on one QALY. This then allows cost-effectiveness acceptability analysis, which is recommended by NICE for health technology appraisals.^14^

In the UK there is no universally agreed cost-effectiveness threshold value. One commonly reported threshold is from NICE in England of approximately £20 000 to £30 000 per QALY.^29^ However, there is a lack of consensus around the appropriate threshold and some argue that it has reduced as expenditure has been constrained.^30–32^ Therefore, the monetary value of simulated QALYs will be varied from £0 to £30 000 to reflect a range of hypothetical willingness to pay thresholds (WTPT).

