#### Handling uncertainty

The estimates of costs and health benefits from the regression analyses will be bootstrapped to simulate 10 000 pairs of incremental cost and QALY outcomes of the MCT intervention.^14^ This captures the relationship between costs and QALYs. The pairs of net costs and QALYs will be plotted on a cost effectiveness plane to illustrate the level of uncertainty in the data.

Each of the net QALY estimates from bootstrap simulation results can be revalued by multiplying it by a willingness to pay threshold. Using these revalued QALY estimates it is then possible to estimate the net benefit statistic (NB) for each pair of simulated net costs and net benefits as:

NB = (O × threshold) – C, where O = net outcome score and C = net cost.

This process will be repeated for the WTPT values of interest to generate a cost effectiveness acceptability curve.

Additional sensitivity analysis will be used to test the impact of the study design on the ICER and results of the cost-effectiveness acceptability analysis. This will include subgroup analysis to estimate the impact of heterogeneity across the population, and scenario analysis to estimate the impact of study design on the cost-effectiveness of intervention. A detailed description of the likely sensitivity analysis and rationale are described in table 2. Note that the sensitivity analysis is informed by data collected in the trial.

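### The cost and QALY regressions are to be chosen from the pooled outcome distribution, which cannot show the link or variance function given covariates; for costs, this can bias the net cost in the ICER

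*Protocol article*

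**What the plan says.** In the Protocol article, under Within-trial analysis, Primary analysis:

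- The motive is the shape of the outcome itself: "Cost and QALY data may not be normally distributed".
- The selection basis follows: "Graphical summaries and descriptive statistics will be used to assess the distribution of the pooled cost and QALY data and identify the appropriate regression models". The example in brackets is "eg, generalised linear model with gamma, log distribution for costs".
- The models are adjusted: "Key covariates will be included in the regression models to control for baseline factors that may influence costs or QALYs".
- Their output is the numerator and denominator of the ICER: "Regression analysis will be used to estimate the net costs and QALYs of MCT".

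Under Handling uncertainty, the same regressions supply the acceptability analysis: "The estimates of costs and health benefits from the regression analyses will be bootstrapped to simulate 10 000 pairs of incremental cost and QALY outcomes".

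Table 2 varies the missing-data approach, 1-month recall data, treatment received, subgroups, benefit measure, value set, MCT cost and time horizon. No row varies the regression family or link.

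**The concern.** The evidence named for choosing the model is marginal, but the model is conditional. The link says how mean cost depends on arm and covariates, and the family says how variance moves with that mean. Right-skewed raw costs arise from a multiplicative model. They arise equally from an additive model with a skewed baseline cost, or from an additive model with skewed errors. A histogram and summary statistics do not separate these.

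The point is about a basis that the article states, not about a diagnostic that it leaves out. Net cost is the numerator of the ICER, which the article makes its primary economic measure. The bootstrap refits the chosen model in each resample, so it carries a wrong mean model into all 10 000 pairs and cannot correct it. Nothing listed in Table 2 would reveal the problem.

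**Working it through.** The article gives no cost mean, SD, skewness or expected net cost, so it has no figure of its own to reproduce. The check is one step of algebra, then simulation on assumed inputs.

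**1. Why the link matters under randomisation.** A log-link model with variance proportional to μ^p solves Σ μ_i^(1−p) (y_i − μ_i) x_i = 0.

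- With p = 1 (Poisson-type), the arm and intercept equations give Σ(y_i − μ_i) = 0 within each arm. Fitted arm means equal observed arm means, so randomisation protects the standardised difference. Linear regression (OLS) has the same property.
- With p = 2 (gamma), they give Σ(y_i/μ_i − 1) = 0 within each arm. This balances ratios, not totals. If the log-linear mean is wrong, the standardised difference (1/n) Σ[μ_i(arm=1) − μ_i(arm=0)] need not equal the true mean difference.
- If the arms have the same cost distribution, the arm coefficient tends to zero whatever the link, so no bias is expected at zero net cost.

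**2. Simulation with a net cost of about £500.** From the article: 332 participants, 1:1. Assumed: gamma baseline cost (shape 0.7, mean £1,500), entered untransformed as the only covariate; additive mean = 1000 + 500×arm + 1.0×baseline; log-link mean = 2200 × exp(0.3(baseline − 1500)/1800) × 1.2^arm; 2000 replicates.

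| Truth | Raw skewness | True net cost | Gamma-log bias (SD) | OLS bias (SD) |
|---|---|---|---|---|
| Additive, gamma errors | 4.4 | £498 | +£185 (£360) | −£12 (£366) |
| Additive, constant variance | 1.8 | £499 | +£201 (£255) | +£2 (£154) |
| Additive, heavy tail | 19.5 | £502 | +£212 (£735) | +£6 (£725) |
| Log link, gamma errors | 8.1 | £470 | −£11 (£281) | −£8 (£325) |

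- Gamma-log bias as a share of its SD in the additive rows: 185/360 = 0.51, 201/255 = 0.79, 212/735 = 0.29.
- Relative to the true value: 185/498 = 37%, 201/499 = 40%, 212/502 = 42%.
- Simulation standard error of each mean is SD/√2000, for example 360/44.7 ≈ £8. The −£11 and the OLS biases are within simulation error.
- Poisson-log biases, in table order, were −£8, +£6, +£13 and −£8, as the algebra predicts.
- With zero true net cost, gamma-log biases were −£6, +£4, +£7 and +£6, all within simulation error.
- The log-link skewness (8.1) lies inside the additive range (1.8 to 19.5), so skewness does not tell them apart.

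**3. Milder inputs.** True additive net cost £250, gamma noise, gamma baseline cost with mean £1,500, 800 replicates.

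- Slope 0.4, baseline CV 1: gamma-log averaged £272 (SD £197), OLS £249 (SD £206). Bias/SD = 22/197 = 0.11. RMSE: √(22² + 197²) ≈ £198 against √(1² + 206²) ≈ £206, so gamma-log is slightly better overall.
- Slope 0.8, CV 1: RMSE about £269 against £277.
- Slope 0.4, CV 1.5: about £212 against £213.
- Slope 0.8, CV 1.5: bias about £138 and RMSE about £362 against £317, clearly favouring OLS. Entering log baseline cost cut the bias to £79 and the SD to £265, so RMSE = √(79² + 265²) ≈ £277, now below OLS.

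**4. Do conditional checks separate the cases?** In further runs at n=332 with a true additive net cost of £250, gamma-log averaged £271 to £504 and OLS £241 to £279; raw costs were right-skewed in every setting. A link test on the fitted gamma-log model rejected it in 25% to 100% of additive datasets, against 6% when the log link was correct. With a correct log link, the SD was £231 for gamma-log and £428 for OLS.

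**5. Scale.** At £20 000 per QALY, a £22 error equals 22/20 000 = 0.0011 QALY and a £212 error 212/20 000 = 0.0106 QALY.

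**The case against.** A reader might infer that the article commits to gamma-log whenever costs are skewed. It does not. Gamma-log is introduced only as an example, no trigger is stated, and nothing excludes checks after fitting. An analysis plan not shown may name them, and their absence from a condensed article is no finding. This stands, and it rules out saying that the primary ICER will be biased. What remains is that the one basis the article gives for identifying the model cannot do that job.

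A reader might also blame the pooling of arms. Pooling is sound, because it keeps the choice blind to the treatment effect. The weakness is looking at the outcome without its covariates. The article already plans pooled regression analyses, but to select covariates, not the link.

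The magnitudes depend on assumptions. The largest need an additive mean, a strongly skewed baseline cost entered untransformed, and a steep slope. The largest precision loss needs near-constant residual variance, which is unusual for health costs. Where variance rises with the mean and the slope and skewness are moderate, bias is small beside sampling error and gamma-log can have the lower RMSE. This stands too, and it means the point is no argument for always preferring linear regression.

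Finally, the selection rule also covers QALYs, but no QALY model is named and no QALY consequence was simulated. The documents support no claim of harm there.

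**Conclusion.** The point holds in limited form. The stated selection basis cannot identify the link or variance function of covariate-adjusted models. If it leads to gamma-log for costs when the mean is closer to additive, the net cost can be biased when the true net cost is not zero. That condition is plausible, since the primary analysis charges staff time and materials to the MCT arm.

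On assumed inputs at n=332, the upward bias ran from about 0.1 of the sampling SD with cost-like variance to 0.3 to 0.8 of it with a steep slope on a skewed baseline cost. With a correct log link, gamma-log was unbiased and more precise than OLS; at zero net cost no bias was seen. No change in a cost-effectiveness conclusion was demonstrated. This is a cheap improvement to the plan, not a defect that invalidates it.

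**What to change.** Replace the selection sentence in the within-trial Primary analysis section so that it says:

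- Selection stays blind to arm. Candidate cost models are fitted to the pooled data with the planned covariates, with arm codes masked or the arm term left out.
- The link for costs is chosen by a link test and by observed against predicted means across the range of predictions. The variance function is chosen by a modified Park test. The functional form of baseline cost is checked at the same time, since it changed the bias materially above.
- Net cost is reported as a standardised mean difference in pounds, whichever link is used.

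Add one row to Table 2 with the alternative model form: covariate-adjusted linear regression with the same bootstrap if a log link is chosen. It is needed as well as the diagnostics, because the link test missed up to three quarters of the additive datasets in the least favourable setting.

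The cost is a paragraph of wording, a few extra model fits, and a second net-cost estimate to report and explain.
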